#### Statistical analyses

For the randomized trial, different analysis sets will be defined including the intent-to-treat (ITT) population (all randomized patients included and analyzed according to the allocated intervention), modified ITT population (mITT: all randomized patients with baseline HRQoL included and analyzed according to the allocated intervention) and per protocol population (PP: eligible patients and analyzed according to the intervention actually received). These three populations will be described according to the following characteristics: compliance with eligibility criteria, epidemiological characteristics, clinical and laboratory characteristics, treatment characteristics, and HRQoL. For the co-primary endpoints, the primary analysis will be conducted in the mITT population, with sensitivity analyses conducted in the PP population. OS will first be compared based on a log-rant test stratified on randomization factors (2% type 1 error rate). Additional analyses will be conducted including Cox regression modeling to provide an estimate of the effect size of the intervention, after checking for underlying model assumptions. For each targeted HRQoL dimension, a *t*-test assuming common variances will be conducted (1% type 1 error rate). Sensitivity analyses assuming a mean difference of 5 points or more for at least one of the targeted HRQoL scores will be conducted. In addition, variance analysis will be conducted for adjustment on randomization factors and additional covariates. Other endpoints will be analyzed using standard statistical techniques. PFS will be analyzed using the same methods as for OS. Censoring mechanisms for the analysis of TUDD will follow recommendations from Bonnetain et al. [28]. With regards to HRQoL data, missing data analysis will be performed to determine the missing data profile. Longitudinal models will be fitted to provide a description of the HRQoL over time and investigate effect of the intervention. For patients treated in the “Case-Management” arm, the analysis of geriatric parameters will involve summary statistics presented at various time-points as well longitudinal analysis to investigate trends over time.

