## Methods/Design

### Objectives

#### Primary objective

The primary objective of the trial is to compare the efficacy of two treatment strategies “usual care” and “Case-management intervention” in elderly cancer patients considered in need of a geriatric assessment (G8 score ≤ 14). Treatment strategies are defined as follows:“Usual care”: Patients are treated according to ongoing standards in oncology.“Case-management intervention”: Patients are treated according to ongoing standards in oncology as in the “Usual care” arm. In addition, patients receive geriatric assessments and interventions coordinated by a geriatrician and a trained nurse, and tailored for the patient.

The intervention content for each arm has been precisely defined by a panel of experts in geriatric oncology. Efficacy will be assessed using a co-primary endpoint encompassing OS and three targeted HRQoL dimensions (global health status, physical functioning and emotional functioning as measured using the European Organization for Research and Treatment of Cancer, EORTC, QLQ-C 30 questionnaire [16]). Specifically, efficacy of the “Case- management intervention” will be considered superior to that of “Usual care” if, at one year, compared to usual care, improvement is observed for OS or at least one of the targeted HRQoL dimensions. We provide additional details of the primary endpoint in evaluation criteria and sample size calculation sections.

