### Eligibility criteria

This study will include patients 70 years and older. In addition, patients must meet the following criteria: performance status 0 to 3 (WHO), candidate to 1^st^ line medical treatment (excluding best supportive care) of breast, colon, rectal, lung, prostate, bladder, or ovarian cancer and lymphomas (indolent and aggressive); excluding exclusive hormonotherapy (except prostate cancer); or, second line medical treatment (excluding Best Supportive Care) of breast, colon, rectal, prostate cancer, ovary and indolent lymphoma.

Exclusion criteria are life expectancy under 6 months, presence of any psychological, familial, sociological or geographical condition potentially hampering compliance with the study protocol and follow-up schedule, participation at the same time in another study in which investigational drugs are used, and patients who have already received two lines of treatment or for whom hormonal treatment (except for abiraterone acetate and enzalutamide in prostate cancer) or best supportive care is indicated.

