The patient will be seen by the geriatrician and the nurse for CGA at baseline (after randomization and before treatment initiation), as well as 6 and 12 months after randomization. The CGA will include the following: questionnaires completed with the nurse (Activities of Daily Living (ADL) [17], Instrumental ADL (IADL), Mini Mental State Examination (MMSE) [18], Mini Nutritional Assessment (MNA) [19], Geriatric Depression Scale (GDS-15) [20], EORTC QLQ-C 30 [16] and the Elderly Cancer Patients version (EORTC QLQ- ELD14) [21]); social evaluation including mode of living, professional help, social situation; geriatric clinical consultation including Timed Up and Go (TUG) [22], Short Performance Physical battery (SPPB [23]), weight loss, subjective health, falls in last 12 months, co-morbidities, other medical treatment, pain (numerical scale) and sleep patterns; geriatric patient management plan defined by nurse and geriatrician. The geriatric management plan establishing any necessary interventions will be defined by the nurse and the geriatrician across eleven intervention areas according to the predefined rules in the *geriatric care protocol.* Table 2 presents a summary of these interventions for the eleven intervention areas: modification of therapy, balancing chronic diseases, pain treatment, nutritional intervention, physical activity, physiotherapy, psychological support, prevention of further cognitive impairment, treatment of sleeping disorders, assistance, and home help. For illustration, with regards to nutritional intervention, weight loss over the last three and six months should be assessed and the MNA questionnaire should be completed. The patient will be considered at risk of malnutrition in case of MNA score between 17 and 23.5 and in such case, advice on increasing dietary uptake (use of food pyramid adapted for elderly patients) should be provided as presented in the *geriatric protocol*. On the other hand, in case of an MNA score below 17, weight loss greater than 5% over the last three months or 10% over the last six months, then the patient will be considered malnourished, and should be referred to a dietician.

**Table 2 Tab2:** Proposed geriatric interventions defined in protocol according to the eleven areas and screening tools used

Area	Indication	Intervention
Modification of therapy	Polypharmacy	• Re-evaluate treatment indications (with general practitioner), optimize treatment according to elderly patient protocols.

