OS is defined as the delay between the date of randomization and the date of death. If the absolute difference in OS at one year is at least 10% greater, then we will consider it as a significant improvement in the OS. For HRQoL, the three targeted dimensions will be assessed using the EORTC QLQ-C 30 questionnaire [16]. Dimensions will be scored according to the EORTC manual [26]. Each dimension will be scored ranging from 0 to 100 and a difference of 10 points or greater will be considered to be clinically significant [27]. If there is a major improvement in at least one of the three scales, without deterioration of the other two, then we will consider as a significant improvement in HRQoL. Secondary endpoints include PFS defined as the delay between the date of randomization and the date of progression or death whichever occurs first. Progression, as well as objective response, will be defined as per the RECIST criteria for solid tumors [28] or the Cheson criteria for lymphomas [29]. HRQoL dimensions other than those targeted for the primary efficacy endpoints will similarly be assessed based on the EORTC scoring manual, and the EORTC ELD-14 module will be assessed following published guidelines [30]. For each of the HRQoL dimensions, time until definitive deterioration (TUDD) will be investigated and defined based on a recent publication [31]. Toxicities will be graded according to the NCI-CTC v4.3 classification. For geriatric questionnaires (G8, ADL, IADL, MNA, MMSE, GDS-15, CIRS-G, TUG), cut-off scores used to define abnormal scores are those reported in the corresponding literature and summarized in Soubeyran et al. [3].

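### The per-protocol sensitivity set is really an as-treated set, and its OS comparison can favour case management when patients who miss the first geriatric visit have a poor prognosis

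*Protocol article*

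**What the plan says.** The Statistical analyses section defines three populations. ITT and mITT both follow allocation; for example "mITT: all randomized patients with baseline HRQoL included and analyzed according to the allocated intervention". The third does not: it is a "per protocol population (PP: eligible patients and analyzed according to the intervention actually received". For the co-primary endpoints, "the primary analysis will be conducted in the mITT population, with sensitivity analyses conducted in the PP population". An ITT set is defined, but that sentence gives it no role.

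Three other statements matter:

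- Under Primary objective, the case-management arm gets the same oncological care as the control arm, and then: "In addition, patients receive geriatric assessments and interventions coordinated by a geriatrician and a trained nurse".
- Under the description of that arm, the geriatric component begins with a "CGA at baseline (after randomization and before treatment initiation), as well as 6 and 12 months after randomization".
- Under Evaluation criteria, "OS is defined as the delay between the date of randomization and the date of death".

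The article does not say what counts as having received an intervention. It gives no number of days between randomisation and the first assessment, and it does not say how a death in that interval is classified.

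**The concern.** A per-protocol set usually keeps adherent patients in the arm to which they were randomised. This one assigns patients to arms by what they received. Because case management is usual care plus something more, a patient allocated to it who never gets the extra component has, on the natural reading, received usual care and is counted there.

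Receipt is settled after the OS clock has started. To be counted as case-managed, a patient must live, and be well enough, to attend the first assessment; no such condition applies to usual care. Early deaths and rapid decliners would leave one arm and be added to the other. That is the pattern of immortal-time bias, and it favours case management.

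At stake is what the sensitivity analysis can show. It should indicate whether the primary OS result is robust. A comparison that leans towards the intervention under the null cannot do that, and agreement with a positive primary result would reassure too much.

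**Working it through.** **The plan's own figure first.** Inputs from the Sample size section: one-year OS 50% v 60%, two-sided 2% error, 85% power. HR = ln 0.6 / ln 0.5 = 0.737. Events = 4(z₀.₉₉ + z₀.₈₅)² / (ln HR)² = 4(2.326 + 1.036)² / 0.305² = 486, as stated. The design inputs are therefore used below as given.

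**Check 1: arithmetic at one year.** Take 600 per arm (1200 randomised 1:1), no true effect and 50% mortality in both arms. Suppose a fraction f of the case-management arm does not receive the component and has one-year mortality m. Both f and m are assumptions. Moving k = 600f patients gives:

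- case management: (300 − km)/(600 − k)
- usual care: (300 + km)/(600 + k)
- difference: f(2m − 1)/(1 − f²)

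| f | m | Case management | Usual care | False gain (points) |
|---|---|---|---|---|
| 5% | 70% | 279/570 = 48.9% | 321/630 = 51.0% | 2.0 |
| 5% | 80% | 276/570 = 48.4% | 324/630 = 51.4% | 3.0 |
| 5% | 90% | 273/570 = 47.9% | 327/630 = 51.9% | 4.0 |
| 10% | 70% | 258/540 = 47.8% | 342/660 = 51.8% | 4.0 |
| 10% | 80% | 252/540 = 46.7% | 348/660 = 52.7% | 6.1 |
| 10% | 90% | 246/540 = 45.6% | 354/660 = 53.6% | 8.1 |

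The design difference is 10 points. The formula gives zero when m = 50%, that is, when non-receivers have the average prognosis.

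**Check 2: simulated log-rank test, counting only deaths before the visit.** 600 per arm, no true effect, 50% one-year survival, follow-up to one year, two-sided 2% level, 4000 runs per scenario. The delay to the visit is assumed. Two hazard shapes were used: constant, and Weibull with shape 1.5. The second has fewer early deaths, as might be expected when life expectancy under 6 months is excluded. Under a constant hazard, the number dying before the visit is 600 × (1 − 0.5^(days/365)), or 7.9, 15.7 and 31.1 at 7, 14 and 28 days. Percentages are tests significant in favour of case management; the nominal rate is 1%.

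| Delay, hazard | Moved | Moved to usual care | Dropped from case management only | Dropped from both arms |
|---|---|---|---|---|
| 7 d, constant | 8 | HR 0.95, 4.3% | HR 0.97, 2.1% | HR 1.00 |
| 14 d, constant | 16 | HR 0.90, 14.5% | HR 0.95, 4.6% | HR 1.00 |
| 28 d, constant | 31 | HR 0.82, 54.3% | HR 0.90, 16.2% | HR 1.00 |
| 14 d, Weibull 1.5 | 3 | HR 0.98, 2.1% | HR 0.99, 1.3% | HR 1.00 |
| 28 d, Weibull 1.5 | 9 | HR 0.94, 4.8% | HR 0.97, 2.8% | HR 1.00 |

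Analysed by allocation, every scenario gives HR 1.00 and about 1% in that direction. At 28 days with constant hazard, the moved set shows one-year OS of 47.6% v 52.7%.

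**Check 3: what drives it.** If 5% miss the component at random (30 patients moved, 2000 runs), HR is 1.00. Moving 31 early deaths gives 0.82. The link with prognosis matters, not the number moved. If, besides a 14-day delay, a random 10% of patients who die before six months also never attend, HR is 0.83.

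**The case against.** Several objections have force.

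- **Receipt is undefined.** The first assessment precedes cancer treatment, so a patient who dies before an on-schedule visit may have received neither strategy. Dropping such deaths from both arms removes the bias. A reader might infer that bias is certain by definition; the text does not go that far. Counting these patients as usual care is the natural reading, not a stated rule. What stands is that the article does fix assignment by receipt, in deliberate contrast to the two sets analysed by allocation, so this is more than a detail left to another document.
- **The size is assumed.** No delay, non-receipt rate or early death rate is given. With few early deaths the effect is small, and with prognosis-neutral non-receipt it is nil. This stands.
- **Eligibility.** A reader might infer a second bias. The geriatric assessment, done in one arm only, examines mood, cognition and social situation, and the entry criteria exclude the "presence of any psychological, familial, sociological or geographical condition potentially hampering compliance with the study protocol and follow-up schedule". Ineligible patients might then be found and removed mainly from case management. The article does not support this. Table 2 treats depression, cognitive impairment and lack of social support as reasons to intervene, and nowhere are assessment findings said to revoke eligibility. Restriction to eligible patients is harmless if judged on pre-randomisation facts without regard to arm.
- **HRQoL.** A reader might extend the point to all four co-primary tests. The HRQoL tests compare scores at one year, and patients who died early have none, so the mechanism does not act on them directly.
- **The trial's conclusion.** The primary analysis is mITT by allocation, and nothing lets the sensitivity result override it. This stands.

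**Conclusion.** The point holds for the OS sensitivity analysis. The set is labelled per protocol but assigns patients by receipt, and receipt of case management depends on reaching a visit after the OS clock starts. On the natural reading, this favours case management whenever non-receipt goes with poor prognosis, which is plausible but not documented in this population.

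Under no true effect, the apparent HR ranges from 0.98 to 0.82 over the assumed delays and hazard shapes, and is 1.00 if non-receipt is unrelated to prognosis. On the one-year scale the false gain is about 2 to 8 points for 5–10% non-receipt and 70–90% mortality among non-receivers. These are illustrations, not predictions. The primary mITT decision is not affected, direct bias in the one-year HRQoL tests is not shown, and differential removal of ineligible patients is not established.

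**What to change.** Redefine the per-protocol population so that patients stay in their randomised arm and none is moved to the other. Judge eligibility only on facts from before randomisation, by the same check in both arms. If non-receivers are to be excluded, use a condition that both arms can meet, such as being alive at a common landmark day with survival counted from that day. Excluding them from case management alone would leave part of the bias, as the second simulation column shows.

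The core change is one sentence in the definition and needs no new data; a landmark also needs its day fixed in advance. The downside is small: patients who switched no longer contribute to the arm they moved to, and a landmark drops early deaths from this sensitivity analysis.

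### The primary OS analysis leaves out randomised patients with no baseline HRQoL form, and no efficacy analysis is assigned to the ITT set

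*Protocol article*

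**What the plan says.** The Statistical analyses section of the protocol article defines three sets.

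- ITT: "all randomized patients included and analyzed according to the allocated intervention".
- mITT: "all randomized patients with baseline HRQoL included and analyzed according to the allocated intervention".
- PP: "eligible patients and analyzed according to the intervention actually received".

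It then assigns them: "For the co-primary endpoints, the primary analysis will be conducted in the mITT population, with sensitivity analyses conducted in the PP population". Under Evaluation criteria, the co-primary endpoint consists of OS and three QLQ-C30 dimensions, so the confirmatory log-rank test at 2% is run in mITT. The one stated use of ITT is descriptive: "These three populations will be described according to the following characteristics". PFS is to be analysed by the same methods as OS, with no set named.

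Evaluation criteria defines OS as the time from randomisation to death.

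On the baseline form, the usual-care section lists QLQ-C30 and ELD-14 in the oncologist's baseline assessment, and the case-management section says that oncologist follow-up is the same in both arms. Case-management patients also complete QLQ-C30 with the nurse at the geriatric assessment: "The patient will be seen by the geriatrician and the nurse for CGA at baseline (after randomization and before treatment initiation").

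**The concern.** A rule about HRQoL data availability decides who counts in a mortality analysis. A patient without a questionnaire still has a usable survival time, so nothing about OS calls for the exclusion.

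The exclusion may not be neutral. Patients here are 70 or older with G8 ≤ 14 and performance status up to 3, and it is reasonable to expect that those who do not complete a form are sicker than the rest. If the form can be completed after randomisation, and one arm has an extra occasion with a nurse to complete it, membership of the primary OS set could depend on the allocated arm. The comparison would then no longer be fully protected by randomisation.

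The planned sensitivity analysis cannot reveal this. PP regroups patients by intervention received and so moves further from the randomised comparison. The analysis that would show the effect of the mITT exclusions is OS in ITT, and the article does not name it.

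**Working it through.** **1. Reproducing the plan's OS figure.** Inputs from the Sample size section: one-year OS 50% versus 60%, two-sided 2% type I error, 85% power, 1096 subjects, 486 events, 1200 randomised.

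- HR = ln(0.60)/ln(0.50) = 0.737, so |ln HR| = 0.305. The article rounds the HR to 0.74.
- Schoenfeld events = 4(2.326 + 1.036)²/0.305² = 486, which matches.
- Mean one-year death rate = (0.50 + 0.40)/2 = 0.45. 486/0.45 = 1080 subjects, within 2% of 1096. Freedman's formula gives 494 events and 1098 subjects. The stated figures are sound.

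**2. Power by share of patients without a form.** Deaths by one year = 1200 × (1 − m) × 0.45, and power = Φ(√D/2 × 0.305 − 2.326). The share m is assumed, because the article gives none.

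| m (assumed) | Patients | Deaths | Power |
|---|---|---|---|
| 0% (ITT) | 1200 | 540 | 88.9% |
| 5% | 1140 | 513 | 87.1% |
| 10% | 1080 | 486 | 85.0% |
| 20% | 960 | 432 | 80.1% |

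Freedman's formula gives slightly lower values: 88.4%, 86.5%, 84.4% and 79.4%.

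**3. Possible bias.** Assume no true effect, with one-year OS of 50% in both arms. If a share p of an arm has no form and those patients have one-year OS s, the retained patients have OS (0.50 − p·s)/(1 − p). All values of p and s are assumptions.

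| p, usual care / case management | s | OS in mITT, usual care / case management | Difference (points) | HR |
|---|---|---|---|---|
| 10% / 5% | 20% | 53.3% / 51.6% | −1.8 | 1.05 |
| 10% / 5% | 40% | 51.1% / 50.5% | −0.6 | 1.02 |
| 15% / 5% | 20% | 55.3% / 51.6% | −3.7 | 1.12 |
| 15% / 5% | 40% | 51.8% / 50.5% | −1.2 | 1.04 |

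With more missing forms in usual care, the error runs against case management. With the imbalance reversed, it favours case management. If p and s are equal in the two arms, the difference is zero.

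**4. Can the form depend on arm?** The two intervention sections together give both arms one common route (the oncologist's baseline) and case management a second route after randomisation (the nurse-led assessment). The article does not say which form defines mITT, nor that it must precede randomisation. Arm dependence is therefore open: neither established nor ruled out.

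**The case against.** The strongest defence is that the common oncologist baseline supplies the form in both arms. If that form is completed before randomisation and alone defines mITT, the exclusion rests on a pre-randomisation variable. The result then applies to a somewhat narrower population, but the arm comparison is not biased. A reader might infer from the post-randomisation nurse visit that the randomised comparison is broken. The documents do not support that; they leave the timing unstated.

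A reader might also infer a loss of planned power, using the 10% non-assessable allowance as the rate of missing forms. The Sample size section does not tie that allowance to baseline forms. Even at 10%, power is 85%, the planned figure, because 1200 was chosen to absorb such losses. This part of the defence stands.

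Third, ITT is not wholly unused: it is to be described with the other sets, and a full analysis plan might use it for secondary endpoints. That is fair, and an unassigned set in a condensed article would be no finding alone. It does not answer the point about OS, where the article itself fixes both the primary and the sensitivity set.

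Finally, patients with life expectancy under six months are excluded, which narrows the group too ill to complete a form. It does not remove it, since performance status 3 is eligible.

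**Conclusion.** The concern holds as a stated choice of the wrong analysis set for OS. The article restricts the confirmatory survival test to patients with a baseline HRQoL form, offers only a treatment-received set as a check, and assigns no efficacy analysis to ITT.

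The certain consequence is that randomised patients with evaluable survival, and their deaths, are excluded for no reason connected with OS: 54 of about 540 one-year deaths if 10% have no form (540 − 486), or 27 if 5% (540 − 513). These counts assume the planning survival rates and the same death rate in excluded patients as in the rest; sicker excluded patients would mean more.

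The possible consequence is bias. Under the assumed values it ranges from 0.6 to 3.7 points, against a target difference of 10, with a sign that depends on which arm lacks more forms. If nearly every patient has a form completed before randomisation, the numerical effect is small. The article does not guarantee that.

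**What to change.** - Make ITT (all randomised, as allocated) the primary set for OS, and state that PFS also uses it.
- Keep mITT for the three HRQoL comparisons, and define it by a baseline form completed before randomisation in both arms, so that a form from the post-randomisation geriatric assessment does not count towards membership.
- Report OS in mITT and in PP as sensitivity analyses, and label PP as a treatment-received comparison.

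Changing the OS and PFS set is a matter of wording. It needs no extra patients or data, since vital status is already part of follow-up, and it retains more deaths. The rule on the timing of the form costs more if sites now collect it after randomisation, because conduct would then have to change. That rule protects the HRQoL set only; OS in ITT does not depend on it.

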### Statistical methods

#### Randomization

For the phase III trial, randomization will be performed on an individual basis based on a 1:1 allocation ratio. Randomization will be stratified by investigational site, treatment line (first or second), and type of cancer (breast, colon, rectal or prostate cancer versus bladder, ovarian, or lung cancer or lymphoma). Because of the number of strata foreseen, randomization by minimization will be implemented [32].

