#### Sample size

Sample size was estimated for the randomized trial. For the null hypothesis we assumed no difference in OS and no difference in the three targeted HRQoL dimensions between the two intervention arms. Alternative hypotheses were two-fold: improvement in OS or improvement in HRQoL. The 5% two-sided type-1 error rate was therefore split between the two alternative hypotheses with 2% for OS and 1% for each of the three HRQoL dimensions. Sample size improvement for testing improvement in OS assumed the following hypotheses: 2% (two-sided) type-1 error rate, 85% power, anticipated 1-year 50% OS rate in the ‘usual care’ group [13], 60% expected 1-year 60% OS rate in the “Case-management” arm (ie anticipated hazard ratio, HR = 0.74). These hypotheses led to an estimated sample size of 1096 subjects (548 per group; 486 events) needed to detect a difference in OS (log-rank test). Sample size for testing improvement in HRQoL was based on a 3% (two-sided) type-1 error. If the intervention is effective, we expect that it will allow us to detect, at one year, a mean difference of 10 points or more for at least one of the three targeted HRQoL scores (common standard deviation of 20 points). Each of the three scales will be independently tested. Five hundred and forty eight subjects per group (as needed for OS comparison) will provide sufficient power (>90%) for independently testing the three HRQoL scales at 1% (2-group t-tests of equal means – common variance).

To anticipate for non-assessable subjects (10%), 1200 patients need to be randomized (ie with G8 score ≤ 14). Based on previous research [5] about 80% of the patients are expected to have positive G8, thus 1500 patients need to be screened for inclusion in the randomized trial.

Since 20% are expected to have normal G8 score, about 300 patients will be included in the parallel cohort. Following our previous experience with the ONCODAGE validation study [3] which included 1668 patients over 18 months, we expect that 800 patients will be screened each year, leading to an expected inclusion period of 1.5 to 2 years. To reach all endpoints, three years of follow-up are required, giving total study duration of 5 years.

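### The 1% test for each targeted HRQoL scale is an unadjusted t-test; an ANCOVA on baseline score and minimisation factors would gain precision at no cost

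*Protocol article*

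**What the plan says.** All references are to the protocol article.

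- **Type 1 error (Sample size).** "The 5% two-sided type-1 error rate was therefore split between the two alternative hypotheses with 2% for OS and 1% for each of the three"; these three are the targeted scales.
- **Planned HRQoL effect (Sample size).** The target is "at one year, a mean difference of 10 points or more for at least one of the three targeted HRQoL scores", with a "common standard deviation of 20 points". The power statement is: "Five hundred and forty eight subjects per group (as needed for OS comparison) will provide sufficient power (>90%) for independently testing the three HRQoL scales". The tests meant are two-group t-tests, each at the 1% level.
- **Primary HRQoL test (Statistical analyses).** For each targeted scale, a t-"test assuming common variances will be conducted (1% type 1 error rate"). No covariate is attached to it.
- **Adjusted analysis (Statistical analyses).** It follows as an addition: "In addition, variance analysis will be conducted for adjustment on randomization factors and additional covariates". The baseline score is not mentioned. Longitudinal models are also planned, to describe HRQoL over time and the effect of the intervention.
- **Analysis set (Statistical analyses).** The co-primary endpoints are analysed in the modified ITT set, which requires a baseline HRQoL assessment.
- **Allocation (Randomization).** "Randomization will be stratified by investigational site, treatment line (first or second), and type of cancer", carried out by minimisation. The OS log-rank test is stratified on these factors.
- **Smaller effect (Statistical analyses).** Sensitivity analyses are planned at a 5-point mean difference.
- **Deterioration (Evaluation criteria).** The same three scales must also show no deterioration before some positive results count as superiority.

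**The concern.** A baseline measure of the outcome is usually its strongest available predictor. The plan makes that measure a condition of entry to the primary set, then does not name it in the test that carries the type 1 error. It also balances the arms on three factors and respects them in the OS test but not in the HRQoL tests, so the two halves of one co-primary endpoint are handled differently.

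Leaving out predictive covariates makes the standard error larger than it need be. Leaving out factors balanced by minimisation also makes the estimated standard error too large for the true variability, so part of a strict 1% is not used. Three of the four primary tests are affected. Because the same scales are used to look for deterioration, lost precision also makes a harm easier to miss.

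**Working it through.** **Inputs from the article.** SD 20; two-sided 1% (z = 2.576); 548 per group; "randomization will be performed on an individual basis based on a 1:1 allocation ratio"; planned effect 10 points; sensitivity value 5 points; one-year survival 50% and 60%.

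**Assumptions not in the article.** The correlation r between the baseline and 12-month score is taken as 0.4, 0.5 and 0.6. The share R² of score variance explained by the minimisation factors is taken as 5%, 10% and 20%. All one-year survivors are taken to be assessed, with SD still 20.

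**1. The plan's own figure.** SE = 20 × √(2/548) = 1.208. Power = Φ(10/1.208 − 2.576) = Φ(5.70), above 99.99%. The stated >90% is reproduced. For 90% power, 2 × (20/10)² × (2.576 + 1.282)² gives 120 per group.

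**2. Expected one-year survivors.** 548 × 0.50 = 274 and 548 × 0.60 = 329. SE = 20 × √(1/274 + 1/329) = 1.636.

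- 10 points: Φ(10/1.636 − 2.576) = Φ(3.54) = 99.98%.
- 5 points: Φ(5/1.636 − 2.576) = Φ(0.48) = 68%.

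**3. ANCOVA on the baseline score.** The residual variance is multiplied by 1 − r², so SE = 1.636 × √(1 − r²). The equivalent gain in assessed patients is 1/(1 − r²) − 1.

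| Assumed r | Variance cut | Equivalent extra patients | SE | 99% half-width (2.576 × SE) | Power, 5 points |
|---|---|---|---|---|---|
| none (t-test) | – | – | 1.636 | 4.21 | 68% |
| 0.4 | 16% | 19% | 1.50 | 3.86 | 78% |
| 0.5 | 25% | 33% | 1.42 | 3.65 | 83% |
| 0.6 | 36% | 56% | 1.31 | 3.37 | 89% |

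By symmetry, the same powers apply to detecting a true 5-point deterioration. At 10 points, power stays above 99.9% in every row.

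**4. If the tested variable is the change from baseline.** Its variance factor is 2(1 − r), so the SE is 1.636 × √1.2 = 1.79, 1.64 and 1.636 × √0.8 = 1.46 at r = 0.4, 0.5 and 0.6. The ratio of ANCOVA variance to change-score variance is (1 − r²)/[2(1 − r)] = (1 + r)/2, which is below 1 for any r below 1. ANCOVA is therefore at least as precise on this reading too.

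**5. Unadjusted test under minimisation.** If the factors are fully balanced, the actual type 1 error is 2 × [1 − Φ(2.576/√(1 − R²))]. This gives about 0.8%, 0.7% and 0.4% at R² = 5%, 10% and 20%. The test is conservative.

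**The case against.** The strongest reply is that nothing is broken. The trial is sized on a t-test and analysed with one. The test is unbiased under randomisation and does not exceed its nominal level under minimisation. At the effect the trial was designed for, adjustment adds essentially no power. All of this stands.

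A second reply is that 5 points is only a sensitivity value. Evaluation criteria treats 10 points as the clinically significant difference. If an observed 10 points is required, a true 5-point effect would reach it in about 0.1% of trials (1 − Φ(5/1.636)), and a smaller SE would not help. The 10-point rule would then bind, not the test, which already reaches significance at about 4.2 points. This stands on that reading, and there the gain would lie mainly in narrower intervals. The article does not say plainly whether the 10 points apply to the observed difference or to the deterioration checks.

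A third reply is that adjustment is already planned, and that the list of additional covariates, which could include the baseline score, is detail a condensed article may leave to the full protocol or SAP. That is fair for the list. It does not move the 1%, which the article attaches to the t-test.

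A reader might also infer more than the documents support:

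- **Two competing primary answers per scale.** No: the t-test clearly holds the type 1 error and the variance analysis is additional.
- **Baseline imbalance is never corrected.** No: a supportive adjusted analysis is planned, although it does not name the baseline score.
- **The test certainly uses raw 12-month scores.** This is the natural reading of a difference at one year, but the article does not exclude a change from baseline.
- **ANCOVA would repair imbalance among 12-month survivors.** It adjusts for measured baseline differences; it cannot be relied on to remove selection by death or dropout.

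**Conclusion.** The point holds as one of efficiency and consistency, not validity. The test carrying the 1% for each targeted scale names no covariates, while the data to adjust it are already in hand and the OS test is stratified on the minimisation factors.

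For the planned 10 points the effect on power is negligible: above 99.9% either way. For a 5-point difference among 274 versus 329 survivors, about 68% power compares with about 78%, 83% or 89% under ANCOVA. The 99% interval half-width falls from about 4.2 to between 3.9 and 3.4 points.

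These gains rest on the assumed correlations of 0.4 to 0.6 and on every survivor being assessed. Missing forms would lower all the 5-point powers. If all 548 per group were assessed, the unadjusted 5-point power would be Φ(5/1.208 − 2.576) = 94%, so the gain would be smaller. The extra loss from omitting the minimisation factors depends on an R² that the article does not give.

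**What to change.** For each of the three targeted scales, make the two-sided 1% test an ANCOVA of the 12-month score on arm, the baseline score of that scale, treatment line and cancer type, with site as a random effect. Keep the unadjusted t-test as a supportive analysis. State explicitly that the 12-month score is the outcome, and fix this before unblinded data are seen.

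The cost is wording only. Baseline QLQ-C30 is collected in all randomised patients by design and the factors are recorded at randomisation, so no extra patients, visits or forms are needed. Deaths and missing 12-month assessments need their own handling, which this change does not supply.
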